The participant plays the exergame by watching their avatar on a 42-inch monitor. The motion capture will use an Astra Pro depth sensor (Orbbec 3D Tech Intl Inc) and the software Nuitrack (3DiVi Inc), which analyzes the data obtained by the sensor to identify the user’s movements. To identify the completed repetitions and errors, the game will have rigidbody colliders in the avatar and in the scenario, passing the avatar positions to the scripts that evaluate whether the movement was correct or not.

One of the advantages of the proposed exergame over conventional therapy is that the game is more stimulating and has a joyful purpose, which provides a form of biomechanical biofeedback—feedback on measurements of movement, balance, postural control, and force output [32]. The exergame will have a dynamic virtual environment to engage participants, which will include elements such as background music, object sounds, avatars demonstrating movements as a form of instruction, sound and visual effects to reward achievements and exercise conclusions, scores, individual progress history, automatic counting of series and repetitions, the possibility of competition between participants, and control of times and turns. Hence, we expect to enhance the gains achieved during therapy, throughout the sessions, and perhaps even in a shorter period, as achieved by Henrique et al [21].

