### Sample, Eligibility, and Allocation

We will recruit 24 participants, exclusively women aged 60 years and over, at the School Clinic of Studies and Professional Practices of the Regional Integrated University of Upper Uruguay and Missions, which is located in Erechim, Rio Grande do Sul, Brazil. The sample size was based on the studies that used a similar methodology to assess the effect of exercise on epigenetic marks and the effect of improved functional mobility induced by running in the older women, related to epigenetic marks [8,9], considering the global H4 histone acetylation levels variable from earlier studies [33,34]. Sample size was calculated using G*Power software [35] considering an effect size of 1.3, two tails, an error probability of .05, and a power of 0.8.

After the invitation to take part in the study, the participants will sign a consent form and complete a demographic questionnaire. The following inclusion criteria will be verified: age 60 years or older; ability to ambulate effectively; absence of any reported diagnosis of neurological, cardiac, or any other disease that restricts physical exercise; absence of depression confirmed by the Geriatric Depression Scale—Short Form [36]; cognitive ability confirmed by the Mini-Mental State Examination, Brazilian version [37]; and acceptance of the commitment not to undergo any other physical therapy during the study.

The sample will have stratified randomization for 2 groups with 12 participants each. Patients will be selected by order of agreement to participate in the study until the number of patients stipulated for either of the groups is reached. The intervention group will practice kinesiotherapy exercises with the exergame, whereas the control group will practice conventional kinesiotherapy exercises without exergaming. Owing to the nature of the intervention, masking of the physical therapists and participants is not possible. However, data will be collected and analyzed by professionals masked to the allocation of the groups.

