### Procedure and Follow-up

During the study, participants in both groups will not be allowed to perform any other type of physical therapy. Intervention sessions for both groups will be carried out twice a week. Each session will last an hour, for 6 weeks, resulting in 12 sessions. This time frame is based on similar studies of Duque et al [42] and Park and Yim [43]. The set of kinesiotherapy exercises was designed based on exercises from successful studies on older rehabilitation [21,44,45], whose movements can be captured by the motion sensor used in the exergame.

We will request all participants to attend sessions wearing dark workout clothes to standardize them and also facilitate body detection by the motion sensor. Each participant will be placed in a room with the setup ready. For the control group, it will be a conventional physiotherapy clinic with the necessary equipment for the exercises. For the intervention group, the environment will contain the same equipment, along with the exergame setup consisting of a 42-inch monitor and the motion sensor.

Both groups will be accompanied by 2 physical therapists throughout the sessions. The professionals will provide instructions and adjust the equipment used in the sessions following a standardized procedure protocol to avoid any type of bias. In the event of an incident (eg, harmful movement, injury, or misuse of equipment), the professional will intervene, pausing the session until the problem is fixed. The session will resume as soon as possible so that the participant can complete the remaining time.

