The intervention group will perform the same procedure and use the same kinesiotherapy equipment as the control group but playing the exergame with its 8 specific exercises as the basis of the session. The exercises will always be performed in the same order and duration, from the first to the last session. During the intervention, there will be a tolerance of only 2 absences per participant, which must be recovered immediately in the same week of the absence. Otherwise, the participant will be removed from the study.

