We expect that both groups have improvements in muscle strength, balance, and cognitive ability, as both of them will exercise. However, due to the motivational and enriching aspects of the exergame, we expect the intervention group to show a significant improvement compared to the control group. We assume that improvement in functional clinical outcomes in the exergame group will be associated with increased BDNF levels and global acetylation of histones H3 and H4. Strategies that modulate BDNF and acetylation levels might be indicated to improve memory in the older population. Many studies have already shown that exercise is a strong epigenetic modulator that increases BDNF levels [7-9,33,62].

Research on this topic is likely to significantly expand the understanding of kinesiotherapy and the impact of exergames for older women. To the best of our knowledge, this may be one of the first studies exploring epigenetic outcomes of exergaming interventions.

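### Removing randomised women from the study for missed sessions leaves them without final outcomes and puts the late between-arm comparison at risk of bias

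*Protocol article*

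**What the plan says.** All references are to the protocol article.

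- **Attendance rule (Procedure and Follow-up).** Each woman may miss at most two sessions. The text then sets the condition for these absences and what follows if it is not met: "which must be recovered immediately in the same week of the absence. Otherwise, the participant will be removed from the study". There are apparently two triggers: exceeding two absences, and not making up an absence within its week. The consequence is leaving the study, not only the sessions.
- **Exposure (Procedure and Follow-up).** "Each session will last an hour, for 6 weeks, resulting in 12 sessions", so an absence can occur at any of 12 sessions, all after allocation.
- **Allocation and size (Sample, Eligibility, and Allocation).** "The sample will have stratified randomization for 2 groups with 12 participants each". The calculation was done "considering an effect size of 1.3, two tails, an error probability of .05, and a power of 0.8". No dropout allowance is listed. Participants and therapists are not masked.
- **Timing (Data Collection).** Blood is drawn at baseline, after the first session and after the whole intervention. Cognition, balance and strength are measured at baseline and after the whole intervention only.
- **Expected mechanism.** Exergame Development says that "the game is more stimulating and has a joyful purpose". The Discussion cites literature that exergames raise exercise adherence in older people, and adds that "due to the motivational and enriching aspects of the exergame, we expect the intervention group to show a significant improvement compared to the control group".
- **Analysis (Statistical Analysis).** The main outcomes are analysed with a gamma generalised estimating equation. Nothing there offsets the removal rule.

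**The concern.** Randomisation makes the two groups of 12 comparable at the start. The rule then drops women because of something that happens afterwards and that allocation can influence. Participants know their arm, and the protocol presents the exergame as more motivating. If the arms lose different numbers of women, or different kinds of women, and attendance is related to outcome, those left at the end are no longer comparable.

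The rule also stops data from being collected. A woman who leaves in week 3 has no late blood sample, Timed Up and Go, dynamometry or cognitive score. A later choice of analysis population cannot recover them. At stake are the late epigenetic marks, balance and strength (primary) and cognition (secondary), in a trial of 24 women with no stated reserve.

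**Working it through.** **1. The plan's own sample size.** Inputs from Sample, Eligibility, and Allocation: d = 1.3, two-sided alpha 0.05, power 0.80, 24 women. The test is not named.

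For a two-sample t test, power = P(|T| > t(0.975, df)), where T is noncentral t with df = n1 + n2 − 2 and noncentrality d·√[n1·n2/(n1 + n2)].

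- 10 per arm: 0.785. 11 per arm: 0.826. The t test therefore needs 22 women.
- 12 per arm: noncentrality 1.3 × √(144/24) = 3.184, df 22, critical value 2.074, power 0.861.
- Mann-Whitney with minimum relative efficiency 0.864 (effective n per arm 12 × 0.864 = 10.37): power 0.801 at 12 per arm, which gives exactly 24.

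The stated 24 is reproduced exactly by the second variant and to within 2 women by the first.

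**2. Power after removals (t test assumed, d = 1.3).**

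| Women left | Removed | Power |
|---|---|---|
| 12+12 | 0 | 0.861 |
| 12+10 | 2, one arm | 0.823 |
| 12+9 | 3, one arm | 0.799 |
| 10+10 | 4, two per arm | 0.785 |
| 9+9 | 6, three per arm | 0.735 |

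Under the Mann-Whitney variant, power starts at 0.801, so any removal takes it below 0.80.

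**3. Shift in one arm's mean.** The documents give neither a removal rate nor a correlation between adherence and outcome, so both are assumed. Take a standard normal outcome and no true difference, and remove the least adherent 2 or 3 of 12 from one arm only.

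The three lowest of 12 standard normal values have expectations −1.629, −1.116 and −0.793. All 12 sum to zero, so at correlation 1 the mean of those left is:

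- 2 removed: (1.629 + 1.116)/10 = 0.274 SD
- 3 removed: (1.629 + 1.116 + 0.793)/9 = 0.393 SD

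Simulation agrees to within 0.002. For correlation ρ, multiply by ρ:

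| Removed from one arm | ρ = 0.2 | ρ = 0.3 | ρ = 0.5 | ρ = 1 (upper bound) |
|---|---|---|---|---|
| 2 of 12 | 0.055 | 0.082 | 0.137 | 0.274 |
| 3 of 12 | 0.079 | 0.118 | 0.197 | 0.393 |

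**4. Removals in both arms.** If a fraction q of the least adherent is removed, an arm's mean shifts by ρ·φ(z_q)/(1 − q).

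- Control 3 of 12 (q = 0.25): 0.424ρ. Exergame 1 of 12 (q = 0.083): 0.167ρ. The difference is 0.257ρ, or 0.05, 0.08 and 0.13 SD against the exergame for ρ = 0.2, 0.3 and 0.5.
- The simulated two-sided type I error in this case is about 0.050 at ρ = 0.3 and 0.062 at ρ = 0.5.
- Equal removal of the same kind of woman from both arms gives zero bias.

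**The case against.** Several points against the concern are sound.

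- **A reader might infer that the trial is biased, or that randomisation is lost for every primary outcome.** The documents do not support that. Bias needs removals that differ by arm and are related to outcome, and no removal rate is given. A supervised six-week programme with make-up sessions may lose few women. The acute blood sample follows the first session, before nearly any absence could lead to removal.
- **A reader might infer that data already collected are thrown away.** The text does not say so. A generalised estimating equation can use the baseline and first-session values of a woman with no final visit, and the analysis population may be set in a plan that is not shown. What does follow from the text is that her final measurements are never taken.
- **A reader might infer that 22 women are needed and 2 are to spare, or that losing 2 breaks the stated power.** The first assumes a t test that the protocol does not name. On that same test, losing 2 from one arm leaves 0.823. The figures of 0.785 and 0.735 need 4 and 6 removals.
- **The shifts are modest** beside the design effect: at correlations of 0.2 to 0.5 they are 0.055/1.3 = 4% to 0.197/1.3 = 15% of it. The larger values of 0.274 and 0.393 SD require absence to pick out exactly the worst responders in one arm.
- **Motivation is not attendance.** The statements about stimulation and motivation could refer to effort within sessions. Only the Discussion mentions adherence, as a general statement from the literature.

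These points limit the size and certainty of the problem but do not remove it. The protocol fixes the rule itself, so this is not a detail left to an analysis plan. Masked assessors do not help, because the selection comes before assessment.

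**Conclusion.** The concern holds as a risk to the end-of-intervention comparison. The protocol requires randomised women to leave the study for non-attendance, which its own rationale gives reason to think allocation may influence, and their late outcomes would then not exist. Late epigenetic marks, balance, strength and cognition are exposed; the acute epigenetic outcome is largely not.

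The size cannot be derived from the documents. With 2 or 3 of 12 removed from one arm and an assumed correlation of 0.2 to 0.5, the shift is about 0.05 to 0.20 SD, with upper bounds of 0.274 and 0.393 SD at correlation 1. The direction is also open. If the exergame does improve attendance and poor attenders do worse, control loses more of its weaker performers and the bias favours control, against the trial's own hypothesis. It reverses if the exergame arm loses more.

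On a t test, power falls below 0.80 after 3 removals from one arm or 4 split evenly. The point needs settling before enrolment, because final measurements not taken cannot be recovered.

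**What to change.** In Procedure and Follow-up, replace removal from the study with the following:

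1. Missed and made-up sessions are recorded for every woman.
2. Every randomised woman is invited to the post-intervention blood draw, cognitive test, Timed Up and Go and dynamometry, whatever her attendance.
3. The main analysis includes all randomised women in the arm to which they were allocated.
4. An analysis limited to women who met the attendance rule is reported as a labelled sensitivity analysis.

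The session attendance and make-up policy itself stays with the investigators; only its consequence for follow-up and analysis changes.

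The cost is about one sentence and a few extra end-of-study assessments. Including poor attenders dilutes the contrast between women who completed the programme somewhat, but the sensitivity analysis still shows it.

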### Data Collection

Blood test values to assess epigenetic marks will be collected from all participants at three stages: at baseline; after the first session of the intervention, to verify the acute effects; and after the complete intervention, to verify the late effects. Cognitive ability, balance, and muscle strength values will also be collected from all participants at two stages: at baseline and after the complete intervention. Game experience data will be collected exclusively from the participants who played the game (intervention group) after the intervention is completed.

### Statistical Analysis

Basic quantitative data will be determined by mean, SD, and median. Categorical data will be determined by simple frequency. Numeric data will be analyzed using statistical software SPSS, version 22 (IBM Corporation). The normality of the data will be tested using the Shapiro-Wilk test. Moreover, depending on the distribution, we will use one-way factor analysis of variance with Tukey post hoc (parametric data), or Kruskal-Wallis test (nonparametric data). To evaluate the main outcomes of the study, a generalized estimation equation with gamma distribution will be performed. To correlate the data, we will apply Spearman and Pearson analyses considering a 95% CI (*P*<.05). All analysis techniques can be adjusted or modified, if required, by the characteristics of the collected data.

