**Methods:**

We will develop a virtual clinic exergame with 8 types of kinesiotherapy exercises. Afterward, we will conduct a 1:1 randomized clinical trial to compare the practice of kinesiotherapy with exergames (intervention group) against conventional kinesiotherapy (control group). A total of 24 older women will be enrolled for 1-hour sessions performed twice a week, for 6 weeks, totaling 12 sessions. We will assess outcomes using epigenetic blood tests, the Montreal Cognitive Assessment test, the Timed Up and Go test, muscle strength grading in a hydraulic dynamometer, and the Game Experience Questionnaire at various stages.

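### Randomisation is stratified, but the named one-way tests cannot include the stratum; used to compare arms on post-treatment values, they would be conservative if the stratification factor is prognostic

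*Protocol article*

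**What the plan says.** Three statements in the protocol article bear on this point.

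- **Allocation** (Sample, Eligibility, and Allocation): "The sample will have stratified randomization for 2 groups with 12 participants each". The section names neither the stratification factor nor the number of strata.
- **Group tests** (Statistical Analysis): depending on the distribution, "we will use one-way factor analysis of variance with Tukey post hoc (parametric data), or Kruskal-Wallis test (nonparametric data". The section does not say which outcomes or which contrasts these tests serve.
- **Main outcomes** (Statistical Analysis): "To evaluate the main outcomes of the study, a generalized estimation equation with gamma distribution will be performed". No model terms are listed, not even arm or time.

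The same section ends by allowing change: "All analysis techniques can be adjusted or modified, if required, by the characteristics of the collected data".

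The sample size rests on global H4 histone acetylation, "considering an effect size of 1.3, two tails, an error probability of .05, and a power of 0.8". Data Collection says that blood markers, cognition, balance and strength are all measured at baseline and again after the intervention; blood is also taken after the first session.

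**The concern.** Stratified allocation balances the arms on a factor, so variation due to that factor no longer contributes to the true sampling error of the arm difference. A one-way analysis does not know this and leaves the between-stratum variation in its residual. The estimated standard error is then larger than the real one, provided the factor predicts the outcome.

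The mismatch lies in what the article states, not only in what it omits. A regression can take a stratum term in a fuller plan, but a one-way ANOVA or a Kruskal-Wallis test could be made to respect the strata only by replacing it with a different method.

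At stake is precision in a trial of 24 women. The 1.3 SD effect was chosen for H4 acetylation. Both arms exercise, and the Discussion expects both to improve, so between-arm differences in Timed Up and Go, strength or cognition could be smaller than 1.3 SD. There, lost precision would matter more.

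**Working it through.** **1. The plan's own figure.** Inputs from Sample, Eligibility, and Allocation: standardised difference d = 1.3, two-sided 5% level, power 0.80. For a two-sample t test with n per arm, the noncentrality is d × √(n/2) on 2n − 2 degrees of freedom.

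- n = 11: 1.3 × √5.5 = 3.05, power 0.826. This is the smallest n that reaches 0.80, so 22 in total.
- n = 12: 1.3 × √6 = 3.18, power 0.861.

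The stated 24 is consistent with this, with two women to spare. The calculation makes no use of strata.

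**2. Assumptions for the check.** The article gives no stratification factor and no prognostic strength. I assume two strata of 12 with 6 women per arm in each, a normal outcome with within-arm SD 1, one post-treatment value per woman, and a stratum that explains a share R² of the within-arm variance.

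**3. Why the one-way interval is too wide.**

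- True variance of the arm difference: (1 − R²) × 2/12, because the strata are balanced.
- Expected within-arm variance estimate when strata are ignored: [11(1 − R²) + 12R²]/11 = 1 + R²/11.
- Ratio of one-way to adjusted interval width: about √[(1 + R²/11)/(1 − R²)] × (2.074/2.080), the last factor being the t quantiles on 22 and 21 degrees of freedom.

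Putting in the numbers:

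- R² = 0.1: √(1.0091/0.9) × 0.997 = 1.056
- R² = 0.2: √(1.0182/0.8) × 0.997 = 1.125
- R² = 0.3: √(1.0273/0.7) × 0.997 = 1.208

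**4. Simulation, 40,000 trials per setting.** Each cell gives the t test on arm alone, then the linear model with arm plus stratum.

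| R² | Size at nominal 5% (arm alone) | Mean 95% CI width, SD | Power at 1.3 SD | Power at 1.0 SD |
|---|---|---|---|---|
| 0 | 0.050 | 1.671 / 1.675 | 0.861 / 0.858 | 0.647 / 0.645 |
| 0.1 | 0.040 | 1.682 / 1.592 | 0.869 / 0.892 | 0.651 / 0.692 |
| 0.2 | 0.029 | 1.690 / 1.498 | 0.882 / 0.924 | 0.654 / 0.739 |
| 0.3 | 0.019 | 1.697 / 1.403 | 0.894 / 0.952 | 0.660 / 0.795 |

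The adjusted model keeps its size at 0.050 to 0.052. For R² of 0.1, 0.2 and 0.3:

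- The width ratios are 1.682/1.592 = 1.06, 1.690/1.498 = 1.13 and 1.697/1.403 = 1.21, in line with step 3.
- The power lost is 2.3, 4.2 and 5.8 points at 1.3 SD, and 4.1, 8.5 and 13.5 points at 1.0 SD.
- At R² = 0, adjusting costs 0.3 and 0.2 points.

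A separate run of 100,000 trials per setting agrees (R² = 0.10: size 0.039, power at 1.3 SD 0.871 against 0.893), and three strata give nearly the same results.

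**5. The same design on change from baseline.** Further assumptions: within-person correlation 0.5, equal SDs at both times, and a stratum effect constant over time. The stratum effect then cancels in the difference. Over R² from 0 to 0.3, size without the stratum is 0.049 to 0.052 and the interval width is 1.67 to 1.68 with or without it. Power at 1.3 SD is 0.860 to 0.863 without the stratum and 0.859 to 0.861 with it. Nothing is lost.

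**The case against.** The strongest reply is that the one-way tests may not be the analysis that matters. The next sentence gives the main outcomes to a GEE, a regression that can carry a stratum term. No outcome is tied to the one-way tests and they are not called between-arm. A Tukey post hoc step has no function with two arms, so they may serve another comparison, such as the three blood-sampling stages. This stands. The point therefore applies only to between-arm comparisons actually made with these tests. One candidate is the Montreal Cognitive Assessment, a secondary outcome measured in both arms, if the main outcomes are taken to mean only the primary ones.

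A reader might infer that the GEE wrongly leaves out the stratum. The article does not support that. It lists no terms at all, and a condensed article commonly leaves a covariate list to the fuller plan. Nor should the conservative size above be carried over to the GEE. A small simulation of a gamma log-link GEE with robust standard errors and an arm-by-time contrast (assumed form, 800 runs per setting, Monte Carlo error about 1 point) rejected a true null 6.5% of the time at R² = 0 and 8.8% at R² = 0.3.

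A reader might also infer that the trial certainly loses power. That is not supported either. The factor is unnamed, its prognostic strength is unknown, and step 5 shows no loss on change from baseline when the stratum effect is constant over time. At the planned 1.3 SD, the unadjusted test keeps about 86% power or more in every setting examined, above the planned 80%.

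The clause allowing techniques to be modified does not settle the matter. It turns on the characteristics of the collected data and does not prespecify adjustment for the strata.

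**Conclusion.** The point holds in conditional form. The article states stratified randomisation and names one-way tests that cannot include a stratum. The mismatch does harm only if three things are true together: the tests are used to compare the arms; they are applied to post-treatment values, or the stratum predicts change; and the factor is prognostic. The error then runs in the conservative direction: a real difference is more easily missed, but false positives are not inflated.

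The size of the harm rests on an assumed R² of 0.1 to 0.3, two equal balanced strata and a Gaussian outcome at one time point. If the factor explains nothing, the loss is nil. Neither an error in the GEE nor a shortfall against the planned 80% power at 1.3 SD is established. This is a low-cost improvement in precision, not a threat to validity.

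**What to change.** In Statistical Analysis, for any between-arm comparison, replace the one-way ANOVA with a linear model containing arm and the factor actually used to stratify the randomisation. Where a rank test is needed, use the stratified (van Elteren) test instead of Kruskal-Wallis. Carry the same factor in the GEE for the main outcomes. The factor and its levels must be named for this to be written, and the article does not currently name them.

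The cost is a sentence or so of wording and one residual degree of freedom per extra stratum level (22 to 21 for a two-level factor). If the factor explains nothing, power falls by less than 0.5 points in the two-stratum check.
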